### Study period

Onboarding is a 6-month period when the implementation and research teams plan the implementation. Intervention is the 12-month period when I-TRANSFER is in operation. Maintenance is a 6-month period when the research team assesses whether the intervention continues without research team monitoring and feedback. The analysis will be an intent to treat. We will adjust for time, or any health system interventions, as well as patient covariates that may confound the findings using generalized mixed models.

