### Conceptual framework

#### Aim 1, effectiveness of the I-TRANSFER intervention

As illustrated in Fig. 1, the Andersen Behavioral Model of Health Services [61] will guide Aim 1. Service use is modeled as a function of health care system factors, and individual determinants. Health services system determinants include resource and organizational factors. Community and market characteristics (e.g., the supply of HHC agencies, physicians, and other health services) are some examples of system resources. Organizational factors include HHC agency and hospital characteristics such as whether the agency is owned by a hospital, part of a chain, or it operates as a for-profit, nonprofit or government entity. The Organizational Readiness for Implementing Change (ORIC) survey results will be a factor in this domain. Implementation determinants (barriers, enablers, strategies) from the CFIR domains discovered in Aim 2 may also be added to the model as variables to understand their impact on the outcomes.

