#### Aim 2, I-TRANSFER implementation

The Consolidated Framework for Implementation Research (CFIR) guides Aim 2 and contains 5 constructs to assess context and implementation determinants at each site. Context has been defined as the set of circumstances or unique factors that surround a particular implementation effort [60] and anything external to the intervention which impedes or strengthens its effects [5, 62]. Determinants are factors that might prevent or enable practice change including barriers, enablers, incentives or disincentives [60, 63]. Processes and strategies are the workflows and interventions applied to address determinants and achieve the implementation [63].

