Implementation of the I-TRANSFER components will be guided by the stakeholders and research team using intervention mapping, as described below. The context and determinants (barriers, enablers), processes, and strategies encountered during Aim 1 will be collected for Aim 2 analysis. Hospital partners will work with the study and HHC team to achieve the following components of I-TRANSFER: identify the sepsis survivors during the hospitalization, make the outpatient follow-up appointment before discharge, notify the HHC agency of a sepsis survivor, conduct timely home health visits and outpatient visits in week one. Based on our preliminary work, we have identified several effective strategies that we can suggest to better identify the sepsis survivor, including generalizable use of sepsis order sets within the electronic health record [14]. We will also recommend use of the Centers for Disease Control (CDC) Epicenters Sepsis Clinical Surveillance Definition, which has the advantage of identifying confirmed cases of sepsis given the criteria of sustained antibiotic delivery [35, 77, 78]. We will examine fidelity to these recommended components as potential implementation enablers.

Challenges we expect to face in making and achieving a timely outpatient visit are limited appointment availability, and patients who cancel or do not attend the visit. A potential strategy is to increase awareness about I-TRANSFER’s evidence and include a script for the clinician to educate the patient about the value and importance of the outpatient visit. Transportation may be an issue as well and will be brainstormed for solutions with the stakeholders and tracked as a barrier. Hospital based personnel will notify the HHC intake department when the patient is a sepsis survivor. The intervention mapping will determine the workflow for this component with each site. It may include phone calls, text messaging, faxed or electronic documents.

HHC intake personnel will likely schedule the nurse visits and notify the visiting nurse of the sepsis diagnosis and date of the outpatient appointment. To meet protocol, the first registered nurse home visit will occur within 2 days of hospital discharge, with a second visit that week. The patient will be encouraged and assisted if necessary (e.g. transportation) to attend their scheduled outpatient appointment.

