### Data sources and collection

#### Aim 1, effectiveness of the I-TRANSFER intervention

A national sample of Medicare administrative, home health OASIS and claims data from CMS Chronic Condition Warehouse (CCW) will be employed (Table 1). This will yield detailed information about the index hospital stay, subsequent HHC and outpatient provider services and outcomes. It also will provide information about the characteristics of hospitals and admitting HHC agencies, and the health care market areas where patients live. The CCW maintains calendar year files so we will request files between 01/01/2021 and 12/31/2024. We will request CCW data on all Medicare beneficiaries with a claim for a HHC service provided one year prior to the start of the study to 6 months after the end. Within these data sets, we will identify the sepsis survivors transitioned from participating hospitals to their partner HHC agency by merging the Provider of Service File with the claim files. The additional sepsis survivors found in the CCW data, not associated with our participating institutions, will serve as additional controls.

**Table 1 Tab1:** Variables Obtained from the Medicare Claims and OASIS Home Health Admission Files

Data	Source
*Physician, Home Health Agency and Hospital Characteristics*	
Physician specialty	Downloadable National Provider Identifier File (CMS)
Home Health Agency and Hospital Ownership	Provider of Services File
Home Health Agency and Hospital Control/auspices (for- profit/non-profit/public)	Provider of Services File
Size of home health agency, # of annual admissions	Provider of Services File
*Beneficiary Sociodemographic, Clinical and Cost Variables*	
Demographics	Medicare Beneficiary Summary File; OASIS
Informal support	OASIS
Living arrangements	OASIS
Eligible for Medicare and Medicaid	Medicare Beneficiary Summary File
Health care use and cost (ie. Medicare program payments)	MedPAR/Medicare Parts A and B SAF claims
Medical diagnoses ICD codes, acute and HHC	MedPAR/Medicare Parts A and B SAF claims; OASIS
Index hospital length of stay	MedPAR
Cognitive, physical, sensory function	OASIS
*Early Nursing and Outpatient Provider Visits Following Index Hospital Discharge*	
Timing and number of home health visits	Medicare Home Health SAF claims
Timing of first physician, physician assistant or nurse practitioner visit for outpatient evaluation & mgt	Mediare Part B SAF claims

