Implementation Mapping. The systematic process of implementation mapping has 5 steps for developing strategies to improve adoption, implementation, and maintenance of evidence-based interventions in the real world [64]. These steps will be informed by the needs assessments, the CFIR interviews with stakeholders and the ORIC survey. Step 1 calls for an implementation needs assessment of eight objectives to identify barriers and enablers, adopters, and implementers (Table 2). At the end of this step, we will know who the champions will be, who will make resources available, and who are the decision makers. In Step 2, together with the dyads, we generate adoption and implementation outcomes and performance objectives, identify determinants, and create matrices of change objectives. This step determines who must do what and how will success be measured. For example, the hospital case managers may be tasked with determining the workflow and strategies for making the follow-up outpatient appointment and educating sepsis survivors on its importance. Matrices of change objectives answer what must change to make something happen [64]. Each performance objective related to I-TRANSFER (e.g., identify the survivors, communicate with HHC, make the appointment, etc.) and its determinants, identified in earlier steps, will be placed on a grid with corresponding person(s) responsible. Third, we will select implementation strategies for each component of I-TRANSFER. In addition to using our teams’ wisdom, we will turn to the literature using resources such as the taxonomy of theory-based methods applicable to individual and organizational levels [70, 79, 81–83]. While the exact strategies to be employed will depend on the findings of this period of data collection, it is likely that they will consist of a multifaceted approach to implementation including staff education via webinar or in-person, changes to organizational processes and workflow, information technology, and the provision of audit and feedback to clinicians and staff taking part in the implementation study. Fourth we will produce implementation protocols, and in the fifth step we will monitor progress and fidelity during the 12-month implementation phase. While maintaining the core I-TRANSFER elements, in keeping with a pragmatic design, we will allow variation in the workflow for dyad preferences while providing monitoring and feedback of the implementation through the rollout [84]. Implementation mapping is an iterative process where steps will be revisited and modified as needed [64].

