In addition to the survivors from the treated dyads in the baseline period, additional control survivors will be used to provide a much larger sample of control observations. These observations will be drawn from the population of Medicare sepsis survivors not being cared for by any of the participating institutions. This sample is unlikely to be balanced on covariates, a priori, with the sample of survivors from participating providers. Therefore, entropy balancing will be used to create sampling weights for these observations to produce balance on covariates. All hierarchical regression analyses will take these entropy balance weights into account. In addition to an intent-to-treat indicator, the regression will include covariates specified by the Andersen Behavioral Model. Inpatient days after the index discharge will be modeled using hierarchical Poisson regression. ED utilization will be modeled using hierarchical logistic regression.

The pragmatic aspects of the study design make it important to conduct various sensitivity and exploratory analyses. Sensitivity analyses will include checks of robustness of findings with and without sepsis survivors who are readmitted shortly after discharge (e.g., within 7 days), those with a resumption of HHC episode, discharges with very short (1 day) or very long hospital stays (30 days or more), and survivors less than 65 years old. Exploratory analyses will include estimation stratified by type of sepsis, sex (as a biological variable), and hospital ownership status.

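### Regression adjustment for health system interventions has no data source in Aim 1 and could not separate a local programme starting near go-live from I-TRANSFER; a non-sepsis comparison at the same dyads would be a useful check

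*Protocol article*

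**What the plan says.** Study period makes the commitment: "We will adjust for time, or any health system interventions, as well as patient covariates that may confound the findings using generalized mixed models". The article does not define these interventions or say where they will be recorded.

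For Aim 1, Data sources and collection lists Medicare claims, OASIS, the Provider of Services file, the Area Health Resources file and Census data. The request itself is broad: "We will request CCW data on all Medicare beneficiaries with a claim for a HHC service". The additional controls are sepsis survivors "not being cared for by any of the participating institutions" (Analysis, Aim 1), weighted by entropy balancing.

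Local context is gathered elsewhere. Study design says: "The context and determinants (barriers, enablers), processes, and strategies encountered during Aim 1 will be collected for Aim 2 analysis". The Aim 2 framework "contains 5 constructs to assess context and implementation determinants at each site". The Aim 1 conceptual framework adds: "Implementation determinants (barriers, enablers, strategies) from the CFIR domains discovered in Aim 2 may also be added to the model as variables". The implementation mapping text, under the ORIC survey heading, expects the I-TRANSFER strategies to include "staff education via webinar or in-person, changes to organizational processes and workflow, information technology, and the provision of audit and feedback".

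Study design also says that the staggered rollout of the earlier stepped-wedge plan is no longer feasible. Study sample gives five hospital and agency dyads.

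**The concern.** The design compares five dyads before and after go-live, with national controls to remove the general trend. What remains open is local history: a hospital-wide readmission programme, a staffing change or an agency-wide scheduling change in the same year. The plan recognises this threat, but the only remedy it states for it is a regression covariate.

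That remedy has three weaknesses:

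- No listed Aim 1 file carries the covariate.
- If the covariate comes from Aim 2, it arrives mixed with I-TRANSFER's own strategies, and adjusting for those could remove part of the effect being measured.
- If a programme starts with I-TRANSFER, the model has little or nothing with which to tell the two apart.

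At stake is whether a fall in readmission can be attributed to I-TRANSFER rather than to something else the same institutions did that year.

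**Working it through.** The plan gives no figure for co-interventions. The yardstick is its target effect: 23% to 16%, 7 points, and 7/23 = 30.4% as stated in Study sample. The sample size calculation is not at issue here.

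**1. Where the covariate could come from.** The Aim 1 files describe patients, providers, market areas and claims; none records local programmes. The Aim 2 surveys, needs assessments and interviews take place at the dyads and concern the implementation of I-TRANSFER. That co-interventions would be known only at the dyads is an inference from these lists, not a statement in the article.

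**2. Whether it could be separated from treatment.** Assumed layout: five equal dyads, 18 months before go-live (12 baseline, 6 onboarding), 12 months after, a common go-live, dyad effects, and time effects taken as known from the large national pool. Let a programme start at go-live in *k* dyads. Within dyads, the squared correlation between the programme and treatment indicators is *k*/5. The variance of the treatment coefficient is therefore multiplied by 1/(1 - *k*/5) = 5/(5 - *k*):

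| *k* | 1 | 2 | 3 | 4 | 5 |
|---|---|---|---|---|---|
| Inflation | 1.25 | 1.67 | 2.5 | 5.0 | not estimable |

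With *k* = 2 and a start three months after go-live, the within-dyad sums of squares are 30 × 0.4 × 0.6 = 7.2 (treatment) and 30 × 0.3 × 0.7 = 6.3 (programme). The cross-product is 9 - 30 × 0.4 × 0.3 = 5.4. The squared correlation is (2 × 5.4)² / (5 × 7.2 × 2 × 6.3) = 0.257, and the inflation is 1.35.

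A second layout used eight quarters, estimated time effects and a single external control unit. It gives 1.04 for one dyad at go-live and 1.5 for a mid-year start in all dyads. A go-live start in all five is again not estimable (rank 14 with 15 columns).

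**3. Bias if the programme is not in the model.** Bias = -(*k*/5) × programme effect, with equal dyads. The programme effects are assumptions.

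- 3 points in 2 dyads: -(2/5) × 3 = -1.2 points; 1.2/7 = 17% of target.
- 3 points in 5 dyads: -3.0 points; 3.0/7 = 43% of target.
- 5 points in 1, 2, 3 or 5 dyads: -1.0, -2.0, -3.0 or -5.0 points (14%, 29%, 43% or 71%).

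Suppose I-TRANSFER has no effect. In a simple comparison of 869 patients per period, two-sided 5% and no clustering, the chance of a significant reduction is 9% for a 3-point programme in two dyads and 33% in all five. Without bias it would be 2.5%.

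**4. Cost in precision of a non-sepsis contrast.** With 869 per period, SE = √[(0.23 × 0.77 + 0.16 × 0.84)/869] = 0.0189, giving power of about 96% for 7 points. Subtracting a non-sepsis change adds variance 2*q*(1 - *q*)/(869*r*), where *q* is the non-sepsis readmission rate and *r* the number of non-sepsis patients per sepsis patient. Neither is in the article; *q* of 12% to 20% is assumed.

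- *r* = 5: SE 0.0202 to 0.0208, power 92% to 93%.
- *r* = 1: SE 0.0245 to 0.0270, power 74% to 81%.

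These figures ignore clustering.

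**The case against.** The strongest reply is that the plan is better protected than this suggests.

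- **Wording.** The Study period sentence speaks of factors that may confound. I-TRANSFER's own workflow changes are the exposure, not a confounder. A reader might infer that this sentence tells the analyst to adjust the effect away; it does not. The concern that strategies enter the model rests on the conceptual framework text, which is optional and meant for understanding their impact on outcomes.
- **Existing checks.** The Discussion plans treatment indicators in the retrospective and onboarding periods, asks sites about such interventions before onboarding, and allows a dyad to be replaced. Aim 2 tests sepsis diagnosis on OASIS and receipt of timely visits; a fall in readmission without movement in these would count against attribution to I-TRANSFER. A reader might infer that nothing in the plan would reveal a competing programme, and that is too strong.
- **Recording.** Programmes at control institutions are part of usual care, so a log is needed mainly at the dyads, where the team has contact.
- **Timing.** No common calendar date for go-live is stated, and a logged programme that starts at another time or in few dyads can be modelled.
- **Scope.** Covariate definitions commonly sit in the analysis plan.

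Much of this stands and limits the point. It does not remove it. The Discussion checks look for early uptake of I-TRANSFER components, not for an unrelated programme starting in the intervention year. A general transition programme could raise timely visits as well. No fuller definition makes a programme separable if it coincides with go-live in every dyad.

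**Conclusion.** The point holds as a limit on attribution that the plan can reduce at modest cost. The stated adjustment has no identified source in the Aim 1 data, may draw on variables that are part of I-TRANSFER, and fails for a local programme that starts at or near go-live in most or all dyads. National controls do not help with that case.

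A reader might go further and conclude that local programmes will be credited to I-TRANSFER unless non-sepsis patients are used. The documents do not support that. Bias requires a programme that exists, starts in the window and affects readmission, and dated logs or leave-one-dyad-out analyses are other partial safeguards.

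The sizes, -1.2 points (two dyads) and -3.0 points (all five), rest on an assumed 3-point programme and equal dyads. The variance figures also rest on a common go-live, which is inferred from the loss of staggering.

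**What to change.** 1. Replace the open-ended reference to health system interventions with those that are dated and documented as independent of I-TRANSFER.
2. Reconcile this with the Aim 1 conceptual framework and the implementation mapping text: keep I-TRANSFER strategies out of the primary effect model and confine them to exploratory models.
3. Prespecify a falsification analysis: the same Aim 1 model fitted to non-sepsis discharges from each partner hospital to its partner agency, against non-sepsis national controls. Report the sepsis effect minus the non-sepsis effect as a sensitivity estimate.

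The home health request already covers all users, so no new patient data should be needed. The cost is analysis work, including a second weighted control set, plus a dated record of programmes at the dyads.

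The check has limits. It cannot detect sepsis-specific programmes. Spill-over of early visits to non-sepsis patients, displacement of their visits, or changed sepsis coding could bias the difference in either direction. It should support the primary estimate, not replace it.

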### Study sample

#### Aim 1, effectiveness of the I-TRANSFER intervention

Sample sizes needed to provide sufficient power were calculated using Stata [79]. Preliminary unpublished data of a national sample show on average a 23% 30-day readmission rate for sepsis survivors in HHC. Our previous study showed a 7-percentage point or 41% relative reduction among those receiving early visits [24], and other studies report that 22–45% of readmissions are preventable [80]. Therefore, to detect a 7-point reduction (30.4% relative decrease) in the readmission rate under the intervention we would require an average of 400 patients per time interval. Current estimates from the sites give us 869 per period.

The I-TRANSFER intervention is targeted at the hospital and HHC agency and is considered part of clinical care implemented for all sepsis survivors. There is no individual patient recruitment, prospective assignment, or primary data collection from patients. The analysis will be completed on existing datasets. We will analyze a sample drawn from all Medicare fee-for-service sepsis survivors discharged to HHC during a 4-year period (01/01/2021 and 12/31/2024). Analyses from our 2013–14 dataset suggests that without exclusions there will be approximately 800,000 sepsis discharges per year who receive HHC [24].

Ten clinical sites located in the United States have committed to participate as dyads, 5 referring hospitals and their 5 partnered home health agencies. Sites were selected based on our relationships with staff, ownership status (hospital owned or free-standing), commitment to appoint an implementation team, size, geography, and diversity (academic and community). We sought regional diversity with sites in the East and West. To be eligible HHC agencies must be Medicare certified to generate claims and confirm a hospital referral source as a partner.

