Physicians must certify the eligibility of patients for HHC, and review and sign the orders for care [46]. Currently, there is no requirement that the physician ordering HHC must see the patient other than the relatively new requirement for a single face-to-face encounter that can be up to 90 days before or 30 days after initiation of HHC services. In general, early outpatient provider visits for patients discharged from acute care vary in timing from 2 days [47] to 30 days [48] and are most effective for those at highest risk [49]. Patients are more likely to attend an outpatient provider visit if scheduled before leaving the hospital [47]. Despite this evidence, our experience is that patients are often expected to schedule outpatient visits themselves. In our studies, for home health patients, outpatient provider follow-up alone, within 7-days, without nursing visits occurred only 24.2% [50] of the time for heart failure patients and 11% of the time for sepsis survivors [24].

Our prior evidence indicates that neither early HHC nursing nor outpatient provider visits alone significantly reduced hospital readmissions in two high-risk populations (heart failure and sepsis). In contrast, when the two practices were combined, early hospital readmissions were significantly reduced. In our prior comparative effectiveness study using national Medicare data and an instrumental variable analysis approach, we found 30-day rehospitalization rates were 7 percentage points lower (41% relative reduction) for sepsis patients when a HHC nursing visit was received within 2 days of hospital discharge, at least 1 more nursing visit the first week, and an outpatient provider follow-up visit by 7 days occurred compared to those without timely follow-up [14, 24].

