Our I-TRANSFER intervention is designed to address several barriers and gaps that may jeopardize the implementation of early post-acute surveillance. Sepsis survivors are not consistently identified with a medical diagnosis of sepsis until after discharge from acute care [51–55]. This results in the diagnosis and other patient characteristics not being adequately communicated to the next level of care [1, 39, 40, 56]. Home health clinicians likely do not know they are receiving a sepsis survivor. Second, there is little evidence to guide the transition of sepsis survivors to HHC. Our protocol is designed to provide a critically needed, especially post-pandemic, best practice intervention model to clinicians and the HHC industry nationwide. This protocol is even more timely given the pandemic, as research suggests that COVID-19 can lead to sepsis [57] and many hospitalized patients prefer to recover at home due to skilled nursing facility capacity and safety concerns [58]. Third, among sepsis survivors transitioned to HHC, and not readmitted within the first week, only 28% received the early visit protocol, shown by our team to be associated with significantly reduced readmissions [24]. This presents an important opportunity to generate further evidence of effectiveness and inform widespread implementation to help many more sepsis survivors. Our advisory group, comprised of national leaders in sepsis care and HHC professional organizations will facilitate widespread dissemination of our findings, from academic nursing and medicine to industry practitioners.

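### The sample-size target is an effect of receiving the visits, used undiluted for an intent-to-treat comparison in which some usual-care patients already receive them

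*Protocol article*

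**What the plan says.** All references are to the protocol article.

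- **Target (Methods, Study sample, Aim 1).** The starting rate comes from national data that "show on average a 23% 30-day readmission rate for sepsis survivors in HHC". The size of effect is taken mainly from the authors' earlier work: "Our previous study showed a 7-percentage point or 41% relative reduction among those receiving early visits". A second support is a literature range of 22–45% of readmissions being preventable. The calculation is then made "to detect a 7-point reduction (30.4% relative decrease) in the readmission rate under the intervention", giving 400 patients per time interval as required and 869 per period as available.
- **Nature of the earlier estimate (Background).** It was obtained "using national Medicare data and an instrumental variable analysis approach". The patients who had the early nursing visits and for whom "an outpatient provider follow-up visit by 7 days occurred compared to those without timely follow-up" form the contrast.
- **Receipt under usual care (Background).** Among survivors sent to home health care and not readmitted in the first week, "only 28% received the early visit protocol, shown by our team to be associated with significantly reduced readmissions".
- **Receipt under the intervention (Study design).** No expected level is given. The anticipated difficulties include "limited appointment availability, and patients who cancel or do not attend the visit".
- **Analysis (Study period; Analysis, Aim 1).** "The analysis will be an intent to treat", and the regression carries an intent-to-treat indicator. Weighted national controls are added to the dyads' own baseline patients.

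**The concern.** The effect of receiving the visits, compared with no timely follow-up, is a different quantity from the change in the readmission rate of a whole population when a programme is switched on. The second is smaller whenever some patients already receive the visits beforehand or some do not receive them afterwards. The article gives reason to expect both, yet the same 7 points serves as the size of both quantities.

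The effect on interpretation is what is at stake. If the stated power refers to a larger difference than the design can be expected to produce, a non-significant result may be taken as evidence that the visits do not work, when the programme may simply have changed receipt too little for the difference to be seen.

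**Working it through.** **Inputs from the article:** average readmission 23%; effect of receipt 7 points or 41% relative; usual-care receipt 28%; 400 required and 869 available per period.

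**Assumptions, because the sample-size paragraph does not give them:** two-sided 5% test, 80% power, equal groups, no clustering; site receipt under usual care equal to the national 28%; receipt under the intervention of 100%, 80% or 60%; all benefit acts through receipt of the full visit combination.

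**Step 1. The plan's own figure.** Two-proportion formula, 23% against 16%:

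n = [1.96·√(2·p̄(1−p̄)) + 0.84·√(p₁(1−p₁)+p₂(1−p₂))]² / (p₁−p₂)² = 502 per group.

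With 400 per group the power is 71%. A one-sided 5% test with 80% power gives 396, close to 400. Since alpha, sidedness and power are not stated, 400 is neither confirmed nor shown wrong for a 7-point difference. With 869 per group the power for 7 points is 96%.

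**Step 2. Two ways to carry the effect over.** A 7-point fall that is 41% relative implies a base near 7/0.41 = 17%, not 23%. The two versions of the effect therefore disagree at 23%, and both need to be shown.

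- *Points.* The 23% is an average that includes the 28% who receive the visits. The untreated risk is 23 + 0.28 × 7 = 24.96% and the treated risk is 17.96%. The intent-to-treat effect is 7 × (receipt − 0.28).
- *Relative.* The untreated risk is 23/(1 − 0.28 × 0.41) = 25.98%. The rate under the intervention is 25.98 × (1 − 0.41 × receipt).

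**Step 3. Results.**

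| Scale | Receipt | Effect (points) | n per group, 80% power | Power, 869 vs 869 | Power, 400 vs 400 |
|---|---|---|---|---|---|
| Points | 100% | 5.04 | 1,006 | 74% | 42% |
| Points | 80% | 3.64 | 1,977 | 46% | 24% |
| Points | 60% | 2.24 | 5,347 | 20% | 12% |
| Relative | 100% | 7.67 | 413 | 98% | 79% |
| Relative | 80% | 5.54 | 825 | 82% | 50% |
| Relative | 60% | 3.41 | 2,263 | 41% | 22% |

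With 869 per group the difference detectable at 80% power is 5.40 points. On the points scale this would need receipt of 0.28 + 5.40/7 = 1.05, which is impossible. On the relative scale about 79% receipt is enough.

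**Step 4. Variations on the points scale.**

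- *National controls treated as free of error:* power at 100%, 80% and 60% receipt is at most about 97%, 78% and 37% (96%, 74% and 34% if the variance is taken at the null rate). In the latter calculation, 80% power needs about 84% receipt.
- *One-sided 5%:* 869 per group gives 83% at full receipt and 58% at 80% receipt; 400 gives 55% at full receipt.
- *If two periods of 869 fall in the intervention year (1,738 per group, an assumption):* 96% at full receipt and 75% at 80% receipt.
- *Clustering:* with 869/5 = 173.8 per dyad and an assumed intraclass correlation of 0.005, a simple design effect is 1 + 172.8 × 0.005 = 1.86, and power for 5.04 points falls from 74% to 48%. This is only an illustration; a before-after comparison within dyads would cancel part of it.

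**The case against.** Several counter-arguments have force.

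- **The available sample does detect 7 points.** With 869 per group the power is 96%. A reader might infer from the dilution that the sample cannot deliver the detection claimed. The arithmetic does not support that: the weakness is in the expected size of the difference.
- **The relative scale is at least as defensible.** The planned 30.4% relative fall is already more modest than 41%. On that scale 7 points is reached at about 94% receipt, so it would be wrong to say that an intent-to-treat analysis could never show it.
- **869 against 869 is not the whole planned comparison.** The regressions add a much larger weighted national sample. The figures in Step 4 are an upper bound, because weighting and clustering cost precision, but they exceed 80% at high receipt.
- **The length of a period is not defined,** so the intervention year may hold more than 869 patients.
- **The preventable-readmission range is a second support,** and 30.4% lies inside it. It does not, however, supply an assumed receipt or an intent-to-treat effect.
- **The dilution formula is simplified.** I-TRANSFER also improves sepsis identification and information transfer, which might help patients who do not complete every visit. The 28% is national and excludes patients readmitted in week one.
- **Receipt is a tested process outcome in Aim 2,** so a null result would be seen beside measured uptake.

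These points limit the size of the problem. They do not remove it: the sample-size paragraph allows neither for receipt under usual care nor for missed visits under the intervention, and it does not bring the national controls into its calculation.

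**Conclusion.** The mismatch is real. An effect among recipients is used, without dilution, as the target of an intent-to-treat comparison, so the stated requirement does not correspond to what the trial estimates. The figure of 400 per interval is below 80% two-sided power at every receipt level examined on both scales, although at full receipt on the relative scale it misses only narrowly (79%). For 869 against 869 the answer depends on assumptions the article leaves open: adequate on the relative scale at about 80% receipt or more, short on the points scale even at full receipt when two-sided.

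It does not follow that the trial is bound to miss any attainable effect. High receipt, the national controls or a longer accrual window could each bring power above 80%. The supported conclusion is that adequate power has not been shown. This should be corrected, but it does not undermine the design. It rests on the national 28% applying at the sites, on the assumed range of receipt, and on benefit acting through the visits.

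**What to change.** Revise the sample-size paragraph as follows:

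1. State the assumed receipt of the full visit combination under usual care at the sites and during the intervention, and whether the earlier effect is carried over in points or as a relative reduction.
2. Derive the intent-to-treat target from those assumptions.
3. Replace the claim of 7 points with 400 patients by the power that 869 per period gives over a range of receipt, for example 60%, 80% and 100%. State alpha, sidedness, the length of a period, the allowance for clustering in five dyads, and how the national controls enter.
4. Say that a non-significant intent-to-treat result will be read beside the receipt measured in Aim 2 and does not exclude a 7-point effect in patients who receive the visits.

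The cost is a rewritten paragraph and a less favourable stated power. No extra patients, new data or change of analysis is needed.
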